#### Spectacle wear periods and washout.

Participants will wear each intervention for a period of six weeks. Participants will be informed that spectacle wear is voluntary and to wear as much as desired. Participants will be advised to avoid wearing coloured spectacle lenses when driving at night as per manufacturer’s specification [52], to ensure that spectral transmission complies with College of Optometrists’ Guidance for Professional Practice on provision of coloured filters when driving [57]. In the unlikely event of adverse event related to spectacle wear whilst driving, incident(s) will be monitored and reported to the project’s chief investigator [name]. Within the first and final week of spectacle wear, participants will be asked to complete a spectacle wear diary online (Research Electronic Data Capture, version 11.0.3, 2021, or paper copy where necessary) at the end of each day of wear. The diary will record the number of hours the spectacles are worn daily. If the participant indicates that they have not worn the spectacles, they will be asked to provide reasons for this. Participants will also be asked to note the number of hours completing concentrated and/or near-work tasks and if the coloured spectacles have been worn to assist with these tasks. Participants will also be asked to grade how helpful (if at all), the spectacle lenses have been in assisting their reading performance on a six point Likert scale (0 = ‘Not at all helpful’ to 5 = ‘Extremely helpful’). Fig 1 comprises a flowchart of the questions that will be posed to participants in their online spectacle wear diary.

**Fig 1 pone.0309625.g001:**
[figure not shown]
Flowchart of spectacle wear diary questionnaire.

After six weeks of wear, a two week washout period will be initiated. Participants’ spectacles will be collected and stored securely. Washout will ensure potential carryover effects from initial spectacle wear will be eliminated. A two week washout period has been determined appropriate, in line with previous investigations [11,37]. Additionally, research suggests colour memory for a chosen colour is the same after 1-hour as it is after 1-week [58]. An overview of trial visits can be seen in the study flowchart in Fig 2.

**Fig 2 pone.0309625.g002:**
[figure not shown]
Randomised control trial efficacy of coloured lenses for visual stress symptoms flowchart.

Upon completion of wear of both interventions a ‘head-to-head’ comparison of both coloured spectacles will take place. Participants will observe a crowded passage of text in a foreign language with both pair of spectacles under masked conditions. Participants will be asked to consider the reading symptoms they experience and to determine which pair of spectacles they find the greatest perceived benefit, irrespective of measures of reading speed and performance noted earlier in the trial. Participants will be advised to wear the preferred spectacles voluntarily, as they require. Participants will be contacted via telephone after three-months to assess long-term spectacle wear compliance and to assess if a sustained benefit from coloured lenses can be determined. Unmasking of participants shall not take place until the three-month follow-up to avoid influencing compliance levels in long-term spectacle wear.

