**Methods:**

This is a double-masked randomised placebo-controlled superiority trial. University students identified with symptoms of visual stress, through use of a reading symptom questionnaire and mid-spatial frequency pattern glare test, will be recruited. Sample size for power of 90% at 5% significance, accounting for 10% dropout will be 65. Participants will be randomly assigned experimental and control coloured spectacle lenses to wear for six weeks followed by a two week washout period, prior to wear of the alternate lenses for a further six weeks with a two week washout period. Participants will compare both sets of spectacle lenses in a ‘head-to-head’ comparison after the secondary washout period, prior to choosing the preferred lenses for voluntary future wear. Long-term adherence to the preferred lenses will be assessed three months post-comparison. Researchers and participants will be masked to spectacle lenses worn throughout the duration of the trial. Reading performance will be assessed with both sets of lenses at various time points within the trial. A range of reading tests, reading symptoms and pattern glare evaluation will be used to monitor change in reading performance and visual stress symptoms during the trial.

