### Study population

#### Sample size calculation.

The Wilkins Rate of Reading Test reading speed has been used as the outcome measure for an improvement with use of coloured filters [12,13,28–31]. Sample size was calculated using statistical software (G-Power, Version 3.19.4, 2024), for an a priori within-factors repeated measures ANOVA of the Wilkins Rate of Reading Test (the primary outcome measure of this trial). A partial eta squared (${\eta \rho }^{2}$) of 0.0355 was used with a conservative small to medium effect size (f) of 0.1985. Probability of a type-1 error (α), of 0.05 and power (1−β) of 0.90 were applied. Correlation among repeat measures was assumed 0.5 and nonsphericity correction (ϵ) was held at 1.0. A sample size of 59 participants was determined appropriate for this investigation The required sample size has been increased by 10% to account for attrition. Therefore, 65 participants shall be recruited for the trial.

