#### Secondary outcome measures: Symptom improvement, reading speed with further reading tests, pattern glare scores and long-term compliance with coloured lenses.

**Reading symptom change:** Prior to commencing wear of coloured lenses, participants will be asked to rate reading symptom frequency on the 6-point Likert scale initially used to recruit participants with symptoms suggestive of visual stress to the trial. After 10 minutes and six weeks of coloured lens wear, participants will be asked to repeat the symptom questionnaire. Additionally, after a two week washout period, participants will be asked to rate reading symptom frequency without the use of coloured lenses.

**Developmental eye movement (DEM) test:** The Developmental Eye Movement Test (DEM) Version 1 (Bernell Ltd, 1987), as summarised by Facchin [62] and Tanke et al. [63], was originally proposed to measure horizontal saccadic function of readers [64] but is now thought to more broadly assess oculomotor function whilst reading [62]. Horizontal and vertical reading speed will be measured. Number of omission, addition, transposition, and substitution errors will be noted and will be used to assist calculating adjusted horizontal and vertical reading speeds A ratio of adjusted horizontal:vertical reading speed will then be determined. The DEM will be completed with and without coloured lenses throughout the trial, owing to the low risk of a learning effect from repeat measures of a test comprising a random series of numbers.

**Test of word reading efficiency (TOWRE):** The Test of Word Reading Efficiency (TOWRE) 1st Edition (Pro-Ed Ltd, Austin TX, 1999) comprises a series of two standardised reading tests which independently assess a participant’s sight-word efficiency and phonemic decoding ability – as discussed further by Torgeson et al. [65]. Reading speed and number of errors made on both subtests will be recorded. A Total Word Efficiency Standard Score will be determined and compared to age-equivalent normative scores and percentiles [65,66]. Reading tests will be completed with and without coloured lenses as detailed in the Schedule of Enrolment.

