### Statistical analyses

The Statistical Package for Social Sciences (Version 29.0; IBM Corporation, USA), software will be used for statistical analysis of reading performance and symptom change with use of ‘experimental’ and ‘control’ precision tints. Kolmogorov-Smirnov tests will be used to assess whether the data follow a normal distribution pattern. Average-measures of Wilkins Rate of Reading Test reading speed performance with the use of ‘experimental’ and ‘control’ lenses will be assessed by repeated measures AVOVA (or the non-parametric equivalent where necessary) testing for both interventions. This will be assessed at three timepoints – baseline measures; initial spectacle collection and after 6-weeks of spectacle wear. Post-hoc analysis using repeated measures ANCOVA testing will be conducted. Covariates in statistical analysis will include: baseline reading speed, the number of errors made in each reading test, number of days spectacle lenses worn, number of hours spectacle lenses worn and number of hours completing concentrated tasks with or without the use of coloured lenses.

Clinically significant improvement noted on the WRRT, will be informed by percentage reading speed improvement with ‘experimental’ lenses, compared to baseline. To date, no validated repeatability values nor defined clinically significant improvement on the test exists in the literature. Therefore, researchers will classify participants’ reading speed improvement by two categories: (i) >5% to 15% improvement; indicating a mild clinical improvement on the WRRT and (ii) >15% improvement; indicating a moderate clinical improvement on the WRRT. These values have been derived from the consensus in the literature, whereby a stricter criterion for reading speed improvement has been applied more recently [3].

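### The three-month telephone call is given the aim of judging sustained lens benefit, but with self-chosen lenses and no comparator it can only describe wear

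*Protocol article*

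**What the plan says.** The relevant text is in the protocol article under Spectacle wear periods and washout, in the paragraph after Fig 2. Once both lenses have been worn, participants view a crowded foreign-language text through each pair, masked, and "determine which pair of spectacles they find the greatest perceived benefit". They may then wear the chosen pair as much as they like. A call at three months has two purposes: to assess compliance with long-term wear, and "to assess if a sustained benefit from coloured lenses can be determined". Participants stay masked until that follow-up.

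Two other places describe the same step more modestly. The abstract (Methods) says "Long-term adherence to the preferred lenses will be assessed three months post-comparison". The heading of the secondary outcome section ends with "long-term compliance with coloured lenses". The aim of showing a sustained benefit appears only in the wear-period section.

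The Study design section makes clear that the control lens is itself tinted and acts as the placebo. Under Randomisation and blinding, what is randomised is which lens is worn first.

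**The concern.** Sustained benefit is an efficacy aim, and the stage it is attached to has no means of testing efficacy. Randomisation governs the two six-week periods and nothing after them. At three months all participants are on a lens selected by their own judgement of benefit, so a favourable report cannot be separated from that selection, from expectation or from change over time. Because the placebo is also a coloured lens, a satisfied placebo wearer would count towards a benefit from coloured lenses.

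What is at stake is a secondary claim. The Discussion expects the results to inform optometric practice, and a wear figure carrying the label of sustained benefit would say more than the data can support.

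**Working it through.** **1. The passages side by side**

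| Place in the protocol article | What the three-month contact is for |
|---|---|
| Abstract, Methods | adherence to the preferred lenses |
| Secondary outcome heading | long-term compliance |
| Spectacle wear periods and washout | compliance, and whether a sustained benefit can be determined |

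**2. What a benefit claim would need, and what this stage has**

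- An assigned comparator at three months: none. Each person wears only the pair they preferred.
- Exposure independent of the outcome: no. The pair is chosen on perceived benefit, and wear is voluntary.
- A pair known to be active: no. The preferred pair can be the control tint.
- Masking: participants stay masked until the follow-up. This protects the wear report but supplies no comparator.

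**3. The number of participants used for illustration**

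The plan gives no figure for the three-month stage, so I use its 59 (65 less the attrition allowance). Inputs from Sample size calculation: "Probability of a type-1 error (α), of 0.05 and power (1−β) of 0.90 were applied"; partial eta squared and f, "of 0.0355 was used with a conservative small to medium effect size (f) of 0.1985"; "Correlation among repeat measures was assumed 0.5 and nonsphericity correction" held at 1.0. From Statistical analyses, the number of measurements is 3: "This will be assessed at three timepoints – baseline measures; initial spectacle collection and after 6-weeks of spectacle wear".

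- f from partial eta squared: √(0.0355 / (1 − 0.0355)) = 0.1919.
- Noncentrality: λ = f² × N × m / (1 − ρ), with m = 3 and ρ = 0.5; df1 = m − 1 = 2; df2 = (N − 1)(m − 1) = 116 at N = 59.
- Result: power 0.901 at N = 59, so the plan's 59 is reproduced. 59 × 1.10 = 64.9, giving the stated 65.
- With the printed f of 0.1985 the same formula needs only 56. That mismatch is a separate matter and does not bear on this point.

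**4. How many could be wearing placebo at three months**

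The protocol gives no share preferring the experimental pair, so the share p is an assumption and the range is shown. Expected placebo wearers = 59 × (1 − p).

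| Assumed p | Expected placebo wearers of 59 |
|---|---|
| 0.50 (no lens effect, even split) | 29.5 |
| 0.60 | 23.6 |
| 0.70 | 17.7 |
| 0.80 | 11.8 |
| 0.90 | 5.9 |

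Unless the preference is very one-sided, a sizeable minority would be in placebo lenses.

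**5. What the masked choice can show**

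Exact binomial test of the number choosing the experimental pair, n = 59, null proportion 0.5, two-sided, everyone stating a choice:

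- 37 of 59 (62.7%): p = 0.067.
- 38 of 59 (64.4%): p = 0.036, exact 95% confidence interval 0.51 to 0.76.

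So 38 is the smallest count above half that reaches two-sided p below 0.05. Unlike the wear rate, this result sets experimental against control directly, under masking.

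**The case against.** The strongest reply is that this is one loosely worded clause. The abstract and the outcome heading already speak only of adherence and compliance. The efficacy hypothesis concerns reading speed and symptoms and is tested in the masked crossover, and no stated analysis turns the call into efficacy evidence. All of this stands, and it limits the point to a secondary aim. It does not remove the clause, which states a purpose that the stage cannot serve.

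A reader might infer more than the document supports:

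- **That experimental and control choosers will be pooled.** Nowhere is this stated, and unmasking at three months would allow a split. Such a split would still compare self-selected groups, so it helps description and not inference.
- **That a no-preference answer is missing, or that the wear rate rests on completers only.** Both would argue from silence in a condensed article whose figures are not shown. The Discussion also commits to reporting drop-outs and losses to follow-up.
- **That the masked choice is wrongly left out.** The secondary-outcome heading and the Statistical analyses section do not name it, but Fig 3 or a fuller document may. It is recommended here as the better use of this step and is not charged as an omission.
- **That the masked choice is a randomised comparison that settles efficacy.** It is a choice within each person; randomisation covers only the order of wear. The experimental tint is also the one the participant picked at colorimetry, and the protocol itself cites evidence that memory for a chosen colour is the same after one week as after one hour. Some choices may reflect recognition or liking.

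**Conclusion.** The point holds for the stated purpose of the call. The three-month contact can describe who goes on wearing which pair, but it cannot determine a sustained benefit. That follows from the design and depends on no numerical assumption. The illustration of about 30 of 59 in placebo lenses assumes no lens effect, an even split and 59 completers; at an assumed 70% preference for the experimental pair it would be about 18. The threshold of 38 of 59 assumes that all 59 state a choice.

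A reader might conclude that the trial's efficacy result is compromised. It is not: the crossover comparison on the primary outcome ends before this stage and is unaffected. The point is worth acting on because it is cheap to correct and because the uncorrected wording invites an efficacy reading of uncontrolled data.

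**What to change.** 1. In Spectacle wear periods and washout, replace the sustained-benefit purpose with a descriptive one: long-term wear at three months, reported separately for those who chose the experimental pair and those who chose the control pair, with no efficacy claim. This brings the section into line with the abstract and the secondary-outcome heading.
2. Name the masked head-to-head choice as a secondary outcome: the proportion choosing the experimental pair, with an exact binomial test against 50% and a confidence interval.
3. State with it that the choice is made within each person and may partly reflect recognition of the tint selected at colorimetry.

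The cost is a change of wording in the outcome and analysis sections. The head-to-head choice and the telephone call are already planned, so no new data are needed. The downside is that the sustained-benefit claim is given up.

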### Outcome measures

An overview of the outcome measures employed at each visit during the trial can be seen in Fig 3.

**Fig 3 pone.0309625.g003:**
[figure not shown]
Schedule of enrolment, interventions and assessment.

#### Primary outcome measure: Wilkins rate of reading test reading speed.

The Wilkins Rate of Reading Test (WRRT) is a long established measure of reading speed with and without the use of coloured filters and has been used in previous reading studies [12,28–31]. As discussed in full by Wilkins et al. [59], the test comprises 15-randomly-ordered monosyllabic commonly used English language words that repeat throughout 10-lines of a size 9-point text to form a crowded paragraph. Owing to the random order of words presented devoid of context, the test isolates the visual input of processing words whilst reading, so that neither syntactic nor semantic reading processes are involved [60].

Participants will read the passage of crowded text aloud within 60-seconds, with and without coloured lenses as detailed in Fig 3 – Schedule of Enrolment, throughout the duration of the trial. The number of words-per-minute (wpm) read correctly will be calculated. During each visit an average reading speed from two measures of the WRRT will be calculated. The examiner will note the number of errors made, namely omissions, reversals, additions, substitutions and mispronunciation [59]. In the event of a ceiling effect whereby all 150 words are read correctly in less than 60 seconds, the time taken to complete the test will be noted, and used to calculate equivalent wpm reading speed [59–61]. The number of additional words read correctly and the percentage reading speed change with coloured lenses will be calculated and compared to baseline measures, in order to assess whether a clinically significant improvement in reading speed has occurred. An increase in reading speed of 15% has been deemed clinically significant by the developer of the Wilkins Rate of Reading test [3]. As percentage change is not normalised, effect sizes and confidence intervals will also be calculated from repeated measures.

#### Secondary outcome measures: Symptom improvement, reading speed with further reading tests, pattern glare scores and long-term compliance with coloured lenses.

**Reading symptom change:** Prior to commencing wear of coloured lenses, participants will be asked to rate reading symptom frequency on the 6-point Likert scale initially used to recruit participants with symptoms suggestive of visual stress to the trial. After 10 minutes and six weeks of coloured lens wear, participants will be asked to repeat the symptom questionnaire. Additionally, after a two week washout period, participants will be asked to rate reading symptom frequency without the use of coloured lenses.

**Developmental eye movement (DEM) test:** The Developmental Eye Movement Test (DEM) Version 1 (Bernell Ltd, 1987), as summarised by Facchin [62] and Tanke et al. [63], was originally proposed to measure horizontal saccadic function of readers [64] but is now thought to more broadly assess oculomotor function whilst reading [62]. Horizontal and vertical reading speed will be measured. Number of omission, addition, transposition, and substitution errors will be noted and will be used to assist calculating adjusted horizontal and vertical reading speeds A ratio of adjusted horizontal:vertical reading speed will then be determined. The DEM will be completed with and without coloured lenses throughout the trial, owing to the low risk of a learning effect from repeat measures of a test comprising a random series of numbers.

**Test of word reading efficiency (TOWRE):** The Test of Word Reading Efficiency (TOWRE) 1st Edition (Pro-Ed Ltd, Austin TX, 1999) comprises a series of two standardised reading tests which independently assess a participant’s sight-word efficiency and phonemic decoding ability – as discussed further by Torgeson et al. [65]. Reading speed and number of errors made on both subtests will be recorded. A Total Word Efficiency Standard Score will be determined and compared to age-equivalent normative scores and percentiles [65,66]. Reading tests will be completed with and without coloured lenses as detailed in the Schedule of Enrolment.

**Adult reading test 2nd edition (ART-2):** The Adult Reading Test 2nd Edition (ART-2) (Adult Reading Test Ltd, Hayling Island, 2017) will provide participants with a ‘naturalistic’ passage of text to be read aloud [67] with and without the use of coloured lenses, as detailed in the Schedule of Enrolment. The test will measure participants’ comprehension and reading speed under timed conditions. Both ART-2 Test 1 passages – ‘News’ (178 words in two paragraphs; Flesch-Kincaid Grade Level 7.9) and ‘Wildlife’ (179 words in four paragraphs; Flesch-Kincaid Grade Level 7.1), will be alternatively presented to participants to avoid a learning effect. Upon initial collection of ‘experimental’ and ‘control’ lenses, participants will be asked comprehension questions on the completed ART-2 passage, to assess conceptual understanding of the passage. Each set of questions will only be asked once throughout the trial at each spectacle collection appointment, to avoid learning effects.

**Low, Mid and high spatial frequency pattern glare test:** The Pattern glare test (Institute of Optometry (i.O.O) Sales Ltd, London, UK, 2003) will measure presence and severity of cortical hyperexcitation with and without coloured lenses. Participants will be asked to focus on the horizontal striped patterns of increasing spatial frequencies (0.3, 2.3 and 9.4 cpd) at a fixed 40 cm viewing distance as per protocol discussed by Evans & Stevenson [46]. Seven questions relating to perceptual distortion visual symptoms experienced will be posed to participants. Total number of symptoms reported will be summed, where normative values >3 on the mid-spatial frequency grating, may indicate diagnosable pattern glare [46]. The series of pattern glare tests will be repeated throughout the duration of the trial to test the hypothesis that optimally selected coloured filters may reduce severity of pattern glare and thus cortical hyperexcitability.

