## Methods and materials

### Study design

This study is designed as a double-masked cross-over randomised placebo-controlled trial of coloured lens efficacy in adults with symptoms of visual stress. The trial design is supported by the Standard Protocol Items: Recommendations for Intervention Trials (SPIRIT) framework (see supporting information S1 File). Participants will be evenly and randomly assigned one of two sets of coloured spectacle lenses for initial spectacle wear for a period of six weeks, followed by wear of an alternate pair of spectacle lenses for a further six weeks. Coloured spectacle lenses will differ in their chromaticity, with the ‘experimental’ coloured lenses, tinted to optimal chromaticity, which are presumed to reduce perceptual distortion symptoms, whilst ‘control’ lenses will comprise a chromaticity similar in perceptual colour appearance to ‘experimental’ lenses, to assist with masking, but differing in chromaticity, such that visual stress symptoms are neither improved nor worsened with use of tint. The ‘Control’ lenses shall therefore act as a placebo. Researchers and participants will both be masked to the spectacle lenses worn. A two week washout between periods of spectacle lens wear will be employed, so that any potential legacy effects of coloured lenses are negated.

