### Recruitment

#### Reading symptoms screening.

A reading symptom questionnaire was developed to screen large cohorts of undergraduate students in lecture theatres (see Supporting Information S2 File). There are currently no validated criteria used to diagnose visual stress [1,3]. Therefore, reading symptoms employed in the questionnaire were devised from symptoms of visual stress reported in the literature such as those proposed by a Delphi study [3] and the ‘Visual Stress Index’ [6]. The questionnaire includes 17-items and 6-point Likert scale with descriptors of symptom frequency (0 = never; 5 = always). Participants will be directed to consider their reading symptoms on a day-to-day basis when completing the questionnaire. Additionally, participants will be provided with a sample of crowded text in a foreign language, devoid of context, to consider when answering the questionnaire, if they are uncertain about the explanation of a particular reading symptom [6].

Questionnaire test-retest reliability was assessed on a sub-group of 115-undergraduate students through repeat issuing of the questionnaire six weeks after initial screening. Participants were blinded to motivation for retesting. High intraclass correlation coefficients were noted (0.91), with low bias of −1.99 (change in symptom scores with repeat measures, with a negative value indicating an increase on total summed symptom score on repeat) by Bland-Altman analysis [34]. Overall questionnaire internal consistency was also considered high by Cronbach’s alpha (α = 0.92) calculations. These findings confirm overall questionnaire test-retest acceptability for screening purposes.

Further questions exploring participants’ ocular and general health will be posed, as well as questions investigating presence of potential visual stress co-morbidities such as; headache [35,36]; formal diagnosis of migraine [37–40]; diagnosis of dyslexia [5,41,42] and/or diagnosis of specific learning difficulties and other general health complaints, known to also be managed with coloured filters [17,43–45].

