Repeated measures ANOVA testing will also assess reading speed on secondary reading tests employed in the trial with both ‘experimental’ and ‘control’ lenses, for the Adult Reading Test (2^nd^ Edition), The Test of Word Reading Efficiency (TOWRE) and the Developmental Eye Movement (DEM) test, at baseline, upon initial spectacle collection and after six-weeks of spectacle wear. Additionally, Friedman test will assess the median change of both interventions on low, mid and high-spatial frequency pattern glare test scores. Furthermore, McNemar’s Test of Proportions will investigate changes in reading symptom frequency scores at both the start and end of the six week spectacle wear period, with both spectacle lens interventions when compared to baseline reading symptoms reported.

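### The symptom rating after 10 minutes of lens wear is not day-to-day frequency, yet it is tested against baseline as if it were

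*Protocol article*

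**What the plan says.** Under Reading symptoms screening, the protocol article describes a 17-item questionnaire on a six-point frequency scale, 0 for never and 5 for always. The frame of reference is given in the same place: "Participants will be directed to consider their reading symptoms on a day-to-day basis when completing the questionnaire".

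The section on secondary outcomes takes this instrument into the trial. Before lens wear, participants are to "rate reading symptom frequency on the 6-point Likert scale initially used to recruit participants". Then: "After 10 minutes and six weeks of coloured lens wear, participants will be asked to repeat the symptom questionnaire". A rating without lenses follows washout.

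Under Statistical analyses, McNemar's test is applied to "changes in reading symptom frequency scores at both the start and end of the six week spectacle wear period", and the comparison is made "with both spectacle lens interventions when compared to baseline reading symptoms reported".

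Two other statements bear on the point. Reliability was checked in 115 students by "repeat issuing of the questionnaire six weeks after initial screening", and the article draws from this only that the form is acceptable for screening. On masking, Study design says: "Researchers and participants will both be masked to the spectacle lenses worn".

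**The concern.** A scale of how often something happens needs a stretch of experience to be rated over. At baseline that stretch is the participant's ordinary reading without the lenses. At six weeks it can be ordinary reading with them. After 10 minutes with newly collected spectacles there is no such stretch, yet the score is treated as a change in symptom frequency and tested.

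Reduced symptom frequency is part of the trial's hypothesis, as stated in the abstract and the Introduction. A significant start-of-wear result would therefore stand beside the six-week result and could be read as support for that hypothesis, although the two ratings do not measure the same thing.

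**Working it through.** The plan gives no figure for this point, and the issue is what a score measures. The check is therefore a comparison of the relevant sections.

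1. **Same instrument at each time.** The secondary-outcome section names the scale used for recruitment and says the questionnaire is repeated. No other form, instruction or recall window is stated for the 10-minute rating.

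2. **What the respondent can draw on.**
   - Before wear: everyday reading without lenses.
   - After six weeks: everyday reading during the wear period.
   - After 10 minutes: a single short sitting. The answer can be a recall of symptoms without lenses, a forecast, or an impression of the reading just done. None of these is day-to-day frequency with the lenses.

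3. **Either instruction leads to a mismatch.** If the day-to-day instruction is kept at 10 minutes, the participant lacks the experience it asks about. If it is replaced by one about the present sitting, the change from baseline subtracts an everyday rating from an in-session rating. In neither case is it a change in day-to-day frequency.

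4. **The score is tested.** The Statistical analyses section names both the start and the end of wear, so the early rating enters a planned test.

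5. **The comparator is baseline.** Each lens is compared with baseline; no experimental-versus-control test of symptoms is stated. Masking and the placebo tint tend to balance expectation between lenses, but they do not remove it from a before-to-after change on one lens. Such a response could appear as improvement on both lenses.

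6. **Reliability evidence.** The intraclass correlation of 0.91 comes from a retest six weeks after screening. It says nothing about a rating made after 10 minutes.

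7. **Link with tint selection.** Under Interventions employed, the experimental tint is chosen because text looks better at once in the colorimeter, and the control tint because it makes no difference. Participants who gain no benefit from any tint are excluded. An immediate impression of the lenses in part asks this selection question again, so a lens contrast at 10 minutes alone would not be strong evidence of symptom benefit either.

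**The case against.** The best defence is that a participant can rate how often a symptom occurred during the reading just done. Most items describe the look of text or refer to reading, and reading tests are also scheduled at spectacle collection, so reading takes place at that visit. This stands: the 10-minute score may carry information about an immediate perceptual effect. It does not make that information day-to-day frequency.

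A second defence is that the day-to-day instruction appears in the screening section, while the form itself (S2 File) and the assessment schedule (Fig 3) are not shown, so a different instruction might be used at 10 minutes. That is possible, but as step 3 shows, it would only move the mismatch to the comparison with baseline.

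Third, the article claims reliability for screening only. That is correct; it does not misuse the coefficient. There is simply no support for the early rating.

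Fourth, the baseline comparator is a weakness at six weeks too. That also stands, and it is why the remedy names the lens contrast at six weeks.

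Three stronger readings are tempting and should not be made:

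- A reader might infer that the 10-minute score will mainly reflect expectation. The documents hold no data on expectation, and the trial is masked with a control tint chosen to look similar. The text supports only that the score is open to it.
- A reader might infer that an early improvement cannot be a real symptom effect. An immediate perceptual effect is possible.
- A reader might count the symptom tests and quote a familywise error rate. The article does not say whether McNemar's test is run on a dichotomised total or item by item, so the number of tests is unknown. Tests on the same people against the same baseline are also unlikely to be independent. Such a figure would not measure the problem raised here.

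**Conclusion.** The point holds in a limited form. The 10-minute rating is at best an immediate impression, is not the same quantity as the baseline or six-week score, and should not be tested against baseline as evidence of reduced symptom frequency. Tested that way for each lens, it is open to expectation or placebo response.

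Its reach is one of two on-lens timepoints of a secondary outcome. The primary outcome, reading speed, is unaffected because speed can be observed on the spot. The six-week rating remains usable. Nothing in the article says that the two ratings would be pooled, or that the early one would be presented as lasting benefit. No numerical size can be given.

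The conclusion assumes that the questionnaire at 10 minutes is the one described for screening, as the article's wording indicates. It needs no assumption about how strong expectation is.

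**What to change.** In the Statistical analyses section, base the symptom efficacy conclusion on the six-week rating, experimental versus control within person. Report the 10-minute rating descriptively for each lens, labelled as immediate impression, and state that it is not evidence of reduced symptom frequency.

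Leave the questionnaire's wording as it is. The article reports 60 participants enrolled of 65 planned, which leaves 65 − 60 = 5 to recruit. A new instruction now would give late ratings a different instrument from those already collected.

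The change needs no new visit or data, only analysis wording. The price is the loss of a formal test at the start of wear.
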